### Outcomes

Primary outcomes measures are: 1) the percentage of participants who drink within the normative limits of the Dutch National Health Council for low-risk drinking, 2) reductions in mean weekly alcohol consumption, and 3) frequency of binge drinking. The secondary outcome measures include the alcohol-related cognitions, attitudes, self-efficacy, and subjective norms.

The Dutch version of the Alcohol Weekly Recall [34] will be used to measure participants’ average glasses of standard alcohol units in the previous week. To assess frequency of binge drinking, respondents will be asked how often they consumed five or more glasses of standard alcohol units on one drinking occasion at least once per month (boys and girls aged 15 to 16 years) and week (men and women aged 17 to 20 years) in the past month and week, respectively.

Attitudes towards alcohol use reflect the extent to which respondents have a positive or negative regard of alcohol use. Respondents will be asked about the perceived effects of alcohol (for example, ‘Drinking alcohol makes me feel less shy’ and ‘Drinking alcohol makes me fat’). Respondents will complete 10 positive and 10 negative attitude items and respond on a 4-point scale ranging from (1) ‘strongly disagree’ to (4) ‘strongly agree’.

Self-efficacy will be measured with a modified version of Young’s Drinking Refusal Self-Efficacy Questionnaire Revised Adolescents Version (DRSEQ-RA: [35,36]), which assesses respondents’ ability to resist drinking alcohol in various situations. This measure was modified by adding additional risk situations in which respondents find it hard to resist alcohol. Additional items were generated by the authors (for example, ‘When I have finished my exams’). Respondents will complete 26 items and respond on a 6-point scale from (1) ‘I am very sure I cannot resist alcohol’ to (6) ‘I am very sure I can resist alcohol’, with higher scores reflecting higher DRSEQ-RA. The measure incorporates three subscales that reflect drinking refusal self-efficacy relating to social pressure (for example, ‘When my friends are drinking’), emotional relief (for example, ‘When I am angry’) and opportunity to drink (for example, ‘When I am watching TV’).

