Descriptive norms will be assessed by measuring perceived alcohol use among best friend, partner, parents, and typical same-sex student. Respondents will be asked about the frequency of their best friend’s/partner’s/parents’ and typical same-sex student’s alcohol use in the previous four weeks. The respondents can respond on a 6-point scale ranging from (1) ‘have not been drinking’ to (6) ‘every day’ [37]. The intensity of their best friend’s/partner’s/parents’/typical same-sex student’s drinking will be assessed by asking the respondents the number of glasses of standard alcohol units their best friend/partner/parents/typical same-sex student had drunk in the previous week in the contexts of at home and outside the home [38]. By asking about these four specific situations, respondents are forced to increase the reliability of response [39]. The scores on these four questions will be summed up to get an indication about the total number of glasses of standard alcohol units the best friends/partner/parents/typical same-sex student of each adolescent consumed in the past week.

Injunctive norms will be assessed by measuring the perceived acceptability of drinking among adolescent’s best friend, partner and typical same-sex student. Respondents will be asked: ‘Do you think that (1) your best friend, (2) your partner and (3) the typical same-sex student would mind if you drink a lot?’ Responses will be coded using a 4-point scale anchored by (1) ‘not at all’ to (4) ‘a lot’. A higher score indicates more liberal norms towards adolescent drinking. Thus, both proximal and distal reference groups will be used to assess social norms.

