### Statistical methods

Descriptive analyses will be conducted to explore whether the randomization has resulted in a balanced distribution of participants’ demographic characteristics across conditions. The potential non-independence of the clustered data, due to the fact that participants are nested in classes, will be taken into account in the analyses.

Data will be analyzed in accordance with the intent-to-treat principle and the completers-only framework in SPSS and/or Mplus. For the intention-to-treat analyses, missing data at follow-up assessments will be handled using multiple imputations using the predictive mean matching method (continuous data) and the logistic regression method (categorical data). Additionally, completers-only analyses will be conducted on participants with scores on all measurements.

Logistic and linear regressions will be performed in both the intention-to-treat and the completers-only analyses to test how the WDYD intervention is related to the alcohol outcomes (that is, heavy drinking, mean weekly alcohol consumption, and frequency of binge drinking) one and six months after the intervention. Besides testing the main effects of the WDYD intervention, moderating effects of age, sex, and drinking status will be investigated to establish whether subgroups are more likely to benefit from the WDYD intervention. Moreover, mediating processes will be examined to: 1) test whether the WDYD intervention modifies the mediating factors (that is, attitudes, social norms and self-efficacy: ASE-model [42]), 2) provide insights into how the WDYD intervention achieves its effects (that is, which mediating factors are modified by the WDYD intervention that are related to alcohol outcomes), and 3) reveal which mediating factors are the most important for realizing change in the alcohol outcomes [43]. Three steps will be performed to analyze the mediating effects [44]. First, it will be analyzed whether the WDYD intervention has an effect on the mediating factors. Then, the effects of the mediating factors on the alcohol outcomes will be analyzed, while controlling for the effect of the WDYD intervention. Finally, it will be analyzed whether or not the size of the mediated effects are statistically significant [44,45].

The study will be performed in accordance with the CONSORT (Consolidated Standards of Reporting Trials) guidelines [46].

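### The injunctive-norm item, its coding and its label contradict each other, so the intervention's effect on this norm and the norm's link with drinking could each be read in the wrong direction

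*Protocol article*

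**What the plan says.** All the conflicting statements stand in one paragraph of the Outcomes section of the protocol article.

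- Construct: "Injunctive norms will be assessed by measuring the perceived acceptability of drinking among adolescent’s best friend, partner and typical same-sex student".
- Item: respondents are asked whether each of the three referents, for example "the typical same-sex student would mind if you drink a lot".
- Coding: "Responses will be coded using a 4-point scale anchored by (1) ‘not at all’ to (4) ‘a lot".
- Direction: "A higher score indicates more liberal norms towards adolescent drinking".

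The score has two uses. Outcomes lists norms among the secondary outcomes: "The secondary outcome measures include the alcohol-related cognitions, attitudes, self-efficacy, and subjective norms". Statistical methods makes social norms one of three mediators. The first mediation aim is to "test whether the WDYD intervention modifies the mediating factors (that is, attitudes, social norms and self-efficacy: ASE-model [42". In the second analysis step "the effects of the mediating factors on the alcohol outcomes will be analyzed, while controlling for the effect of the WDYD intervention", and the third step tests whether the mediated effect is significant.

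**The concern.** To mind someone's drinking is to disapprove of it. With the anchors given, the top code marks the strongest perceived disapproval, yet the label calls the top code the most liberal norm. The item and coding cannot both stand beside the label unless a recoding step lies between them, and the article states none.

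What is at stake is the direction of a result. If adolescents in the experimental condition come to believe that their friends would object more, the coded score rises. A reader who follows the label would report that norms had become more permissive. The mediation analysis is meant to explain how the intervention works, so a misread direction affects the very thing it is meant to deliver.

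**Working it through.** The plan gives no figure to reproduce here. The check has two parts: the direction of the scale, and what a reversed scale does to the planned models.

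**1. Direction of the scale** (inputs: item, anchors and label from Outcomes)

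| Code as written | Meaning from item and anchors | Meaning by the label | 5 - code |
|---|---|---|---|
| 1 | would not mind: most liberal | least liberal | 4 |
| 2 | between | between | 3 |
| 3 | between | between | 2 |
| 4 | would mind a lot: least liberal | most liberal | 1 |

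The second and third columns run in opposite directions. The transformation 5 - code brings the score into line with the label.

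**2. Effect on the planned models**

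Let T be condition, M the norm score as coded and Y an alcohol outcome.

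- Path a: M = i + aT + error
- Path b and direct effect c': Y = j + c'T + bM + error

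Put M* = 5 - M.

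- M* = (5 - i) - aT - error, so a* = -a.
- Substituting M = 5 - M* gives Y = (j + 5b) + c'T - bM* + error, so b* = -b and c' is unchanged.
- Mediated effect: a*·b* = (-a)(-b) = ab.

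The standard errors of a and b do not change either, so the test of the product gives the same result. For the binary low-risk-drinking outcome the same substitution applies in the linear predictor of the logistic model.

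**3. Numerical illustration**

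These are simulated data with assumed values, chosen only to show the signs: 750 independent respondents, 375 per arm; an underlying disapproval scale shifted by 0.3 SD in the experimental arm and cut into four categories; an outcome falling by 1.5 per scale point, with a direct effect of -0.5 and residual SD 5.

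| Scoring | a | b | a·b | direct |
|---|---|---|---|---|
| as coded | +0.397 | -1.703 | -0.677 | -0.269 |
| 5 - code | -0.397 | +1.703 | -0.677 | -0.269 |

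(The products come from unrounded coefficients.)

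**4. What the reader would be told**

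The first row of that table, read correctly, says that the intervention raised perceived disapproval and that more disapproval went with less drinking. Read by the label, the same row says that the intervention made norms more liberal and that more liberal norms went with less drinking. The mediated reduction of 0.677 is the same in both accounts, but the explanation is reversed.

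**The case against.** The strongest reply is that the label describes the final scale score, and that the article gives the raw answer anchors and leaves out a recoding step. The stated construct is acceptability, which agrees with the label. A condensed article may leave scoring detail to a fuller document that is not shown. On that reading no result would be inverted and only the description is at fault.

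Part of this stands. The document cannot show which of the three elements is mistaken, or that the data will be analysed as coded, so the misreading is conditional. But the coding sentence says how responses will be coded, and the direction follows at once. The article chose to state item, coding and direction, and they conflict. That is a wrong statement, not an omitted detail.

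The objection also rightly limits two stronger readings. A reader might infer that the mediated effect itself would come out with the opposite sign. It would not, because both component paths flip and their product does not. A reader might also infer that the whole social-norms domain is affected. Outcomes measures descriptive norms separately, by the perceived frequency and quantity of others' drinking, and their direction is not in doubt.

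**Conclusion.** The scoring rule for injunctive norms is wrong as written. Used exactly as stated, it would reverse the reading of the intervention's effect on a component of a secondary outcome, and of both component paths through a planned mediator. This concerns three items at every assessment at which they are used. Absolute sizes do not change.

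The sign, size and significance of a·b, the direct effect, the descriptive norms, the three primary outcomes and the sample size are all unaffected.

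The textual conflict is certain. The consequence rests on two conditions: that the score is analysed as coded, and that it is interpreted by the label. The invariance of a·b assumes that the injunctive score enters the models on its own. The article describes no composite with the descriptive norms.

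**What to change.** Settle which direction the analysed score has, then state one of the following in Outcomes:

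- the three injunctive items are reverse-coded as 5 minus the response before scoring, so that a higher score means more liberal norms; or
- the coding stays as it is, and a higher score means less liberal (more disapproving) norms.

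Use the chosen direction in the secondary-outcome analysis and in every step of the mediation analysis, and name it in the tables that report paths a and b.

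The cost is one line in the scoring rules. No new data, change of design or change of sample size is needed.

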### Sample size

The power calculation of our study reflects the notion that we aim to detect an increase in the percentage of participants showing low-risk drinking after one month of 42% in the experimental group versus 31% in the control group [40]. A total sample size of 750 respondents (n = 375 per condition) will be required to test the hypothesis in a two-sided test at alpha = 0.05, a power of (1-beta) = 0.80, and expecting a worst-case scenario of totally 15% loss-to-follow-up after randomization. The fact that the data are clustered (participants are nested in classes) was taken into account in the power calculation. The intraclass correlation is expected to be between 0.03 and 0.06 indicating that there is a low degree of similarity between participants within classes [41].

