## Methods/design

### Trial design

The effectiveness of the What Do You Drink web-based brief alcohol intervention will be tested in a two-arm parallel-group cluster randomized controlled trial. Participants comprise approximately 750 heavy-drinking adolescents with a low educational background aged 15 to 20 years: 375 are in the experimental condition (web-based brief alcohol intervention) and 375 are in the control condition (no intervention).

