### Randomization

Randomization will occur by class level within the educational institutions to avoid contamination between the conditions. Thus, classes of adolescents from a VMBO or MBO institution will be randomly assigned to either the experimental or the control condition. A blocked randomization scheme (block size four) will be used. An independent researcher of the Behavioural Science Institute will perform the allocation with a computerized random number generator after baseline assessment.

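### The 80% power claimed for 375 per arm with class clustering holds only at about two to three analysed pupils per class, which the protocol neither states nor supports

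*Protocol article*

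**What the plan says.** All of the power statement is in the Sample size section of the protocol article. The target is "low-risk drinking after one month of 42% in the experimental group versus 31% in the control group", with a "two-sided test at alpha = 0.05, a power of (1-beta) = 0.80", and "expecting a worst-case scenario of totally 15% loss-to-follow-up after randomization". From these it concludes: "A total sample size of 750 respondents (n = 375 per condition) will be required". It then says of clustering: "The fact that the data are clustered (participants are nested in classes) was taken into account in the power calculation". The only clustering input is the ICC: "The intraclass correlation is expected to be between 0.03 and 0.06 indicating that there is a low degree of similarity".

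The Randomization section confirms the unit: "Randomization will occur by class level within the educational institutions to avoid contamination between the conditions". The Trial design section confirms equal arms of 375.

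The article gives no number of classes, no expected number of eligible pupils per class and no design effect. The Procedure and participants section limits the study sample to pupils aged 15 to 20 who report heavy drinking and are willing to change. Those with an AUDIT score of 20 or more, or in treatment for alcohol-related problems, are excluded. The number analysed per class is therefore smaller than the class roll.

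**The concern.** When classes are randomised, the sample size for individual randomisation must be multiplied by the design effect, DE = 1 + (m − 1) × ICC, where m is the number analysed per class. A low ICC does not make DE small: at m = 10, an ICC of 0.03 to 0.06 gives 1.27 to 1.54. The stated total should therefore sit well above the individually randomised figure plus loss, unless m is tiny. It appears to sit on that figure.

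This is the article's only power calculation, and it concerns a primary outcome. If the true power for an 11-point difference is below 80%, a null result would be read as stronger evidence against the intervention than the design can give.

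**Working it through.** **Inputs (Sample size section):** p1 = 0.42, p2 = 0.31, difference 0.11, mean proportion 0.365; two-sided alpha 0.05 (z = 1.960); power 0.80 (z = 0.842); 15% loss; ICC 0.03 to 0.06; 375 per arm. **Assumption:** m is not stated, so a range is shown.

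**Step 1. Individual randomisation, no continuity correction.**
n = [1.960 × √(2 × 0.365 × 0.635) + 0.842 × √(0.42 × 0.58 + 0.31 × 0.69)]² / 0.11²
= (1.3344 + 0.5693)² / 0.0121 = 299.5, so 300 per arm.
300/0.85 = 352.9, so 353 per arm after loss.

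**Step 2. The same with continuity correction.**
n' = (299.5/4) × [1 + √(1 + 4/(299.5 × 0.11))]² = 317.4, so 318 per arm.
318/0.85 = 374.1, so **375 per arm, 750 in total**. This is the protocol's figure, reached with DE = 1.

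**Step 3. Largest design effect that 375 can carry.** Evaluable per arm: 375 × 0.85 = 318.75.
- With continuity correction: 318.75/318 = 1.00. Nothing remains.
- Without it: 318.75/300 = 1.0625. Then m = 1 + 0.0625/ICC = 3.1 at ICC 0.03, or 2.0 at ICC 0.06.

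Other two-sided formulas leave similarly little. The arcsine method also gives 300, and the unpooled-variance method gives 297 (350 after loss).

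**Step 4. Power at the planned size.** Effective n per arm = 318.75/DE, no continuity correction, 15% loss.

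| m (assumed) | DE, ICC 0.03 | Power | DE, ICC 0.06 | Power |
|---|---|---|---|---|
| 2 | 1.03 | 81.3% | 1.06 | 80.2% |
| 3 | 1.06 | 80.2% | 1.12 | 78.0% |
| 5 | 1.12 | 78.0% | 1.24 | 73.7% |
| 10 | 1.27 | 72.7% | 1.54 | 64.3% |
| 15 | 1.42 | 67.9% | 1.84 | 56.7% |
| 20 | 1.57 | 63.5% | 2.14 | 50.5% |

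At m = 4, DE is 1.09 to 1.18 and power 79.1% to 75.8%, so both ends of the ICC range are below 80% from m = 4 upward. If m = 10 means ten enrolled and 8.5 analysed after loss, power is 74% to 67%.

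**Step 5. Difference detectable at 80% power** (control 31%, same method). For m = 5 to 20 it is 11.3 to 13.4 points at ICC 0.03 and 11.9 to 15.8 points at ICC 0.06, against the planned 11.

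**Step 6. What m = 2 to 3 would imply.** 750/3 = 250 classes; 750/2 = 375 classes.

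**The case against.** A reader might infer from Step 2 that clustering was left out altogether. The document does not establish that. It names no formula and no continuity correction, and the match is not unique: 300 × 1.06/0.85 = 374.1, which also rounds up to 375. A DE of 1.06 follows from m = 3 at ICC 0.03 or m = 2 at ICC 0.06, both within the stated range. Clustering may have been included with a very small cluster size. This objection stands.

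A reader might also take the lower rows of the table as the trial's actual power. That is not supported either. The eligibility filters make m smaller than the class roll by an unknown amount, and nothing in the article points to 15 or 20 eligible pupils per class.

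Three further points deserve weight:
- The 15% loss is called a worst case. With 5% loss the covered DE is 375 × 0.95/300 = 1.19 (m about 7 at ICC 0.03, 4 at 0.06); with none it is 375/300 = 1.25 (m about 9 and 5). But the article claims 80% at 15% loss, and that is the claim tested here.
- An article may leave cluster details to the full protocol. The absence of m is therefore not the point. The article asserts that clustering is inside 750, and its own figures allow this only for a very narrow range of m.
- The Statistical methods section says the analysis will account for clustering. That protects the type I error rate but does not restore power. Baseline adjustment might recover some, but the sample-size text does not invoke it.

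Calling an ICC of 0.03 to 0.06 low is ordinary wording and not an error in itself.

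**Conclusion.** The concern holds in a conditional form. With the article's own inputs, 375 per arm is either the individually randomised size with no design effect, or a size that allows a design effect of at most 1.06. No two-sided calculation tried here reaches 375 with more than about three analysed pupils per class at 15% loss. The article states no such number. It describes heavy drinking as particularly common in this group and asks institutions to enter as many classes as possible; neither statement supports two to three eligible pupils per class.

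At m = 4 or more, power is below 80% at both ends of the stated ICC range. It is 78% to 74% at m = 5 and 73% to 64% at m = 10. These figures rest on an assumed m, 15% loss and no continuity correction, which is the more favourable choice. The size of the shortfall is therefore uncertain. That the 80% claim is unsupported outside m of about 2 to 3 does not depend on which m is chosen.

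**What to change.** Keep 750 participants. Base the calculation on the number of eligible pupils expected per class after the filters in Procedure and participants, and on the number of classes. Give DE = 1 + (m − 1) × ICC at both 0.03 and 0.06, and name the formula, including whether a continuity correction is used. Then replace the stated 80% with the resulting power, or with the difference detectable at 80% power. If an expected cluster size of about 2 to 3 can be shown, state it with the number of classes it implies; the 80% can then stand for the ICC values at which it holds (both at m = 2, only 0.03 at m = 3).

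The cost is a rewritten paragraph and, in all likelihood, a less favourable stated power. No extra participants are needed.

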### Randomization

Randomization will occur by class level within the educational institutions to avoid contamination between the conditions. Thus, classes of adolescents from a VMBO or MBO institution will be randomly assigned to either the experimental or the control condition. A blocked randomization scheme (block size four) will be used. An independent researcher of the Behavioural Science Institute will perform the allocation with a computerized random number generator after baseline assessment.

### Statistical methods

Descriptive analyses will be conducted to explore whether the randomization has resulted in a balanced distribution of participants’ demographic characteristics across conditions. The potential non-independence of the clustered data, due to the fact that participants are nested in classes, will be taken into account in the analyses.

Data will be analyzed in accordance with the intent-to-treat principle and the completers-only framework in SPSS and/or Mplus. For the intention-to-treat analyses, missing data at follow-up assessments will be handled using multiple imputations using the predictive mean matching method (continuous data) and the logistic regression method (categorical data). Additionally, completers-only analyses will be conducted on participants with scores on all measurements.

Logistic and linear regressions will be performed in both the intention-to-treat and the completers-only analyses to test how the WDYD intervention is related to the alcohol outcomes (that is, heavy drinking, mean weekly alcohol consumption, and frequency of binge drinking) one and six months after the intervention. Besides testing the main effects of the WDYD intervention, moderating effects of age, sex, and drinking status will be investigated to establish whether subgroups are more likely to benefit from the WDYD intervention. Moreover, mediating processes will be examined to: 1) test whether the WDYD intervention modifies the mediating factors (that is, attitudes, social norms and self-efficacy: ASE-model [42]), 2) provide insights into how the WDYD intervention achieves its effects (that is, which mediating factors are modified by the WDYD intervention that are related to alcohol outcomes), and 3) reveal which mediating factors are the most important for realizing change in the alcohol outcomes [43]. Three steps will be performed to analyze the mediating effects [44]. First, it will be analyzed whether the WDYD intervention has an effect on the mediating factors. Then, the effects of the mediating factors on the alcohol outcomes will be analyzed, while controlling for the effect of the WDYD intervention. Finally, it will be analyzed whether or not the size of the mediated effects are statistically significant [44,45].

The study will be performed in accordance with the CONSORT (Consolidated Standards of Reporting Trials) guidelines [46].

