From the participating institutions, none of the adolescents will be excluded from study participation to avoid stigmatization and social exclusion. However, after the recruitment and enrolment of the institutions in the trial, an online baseline assessment will be carried out to establish whether the adolescents of the participating classes can be included in the study sample. Therefore, participants must: 1) be between 15 and 20 years old, 2) report heavy drinking in the past six months, and 3) be willing to change their alcohol consumption. Our definition of heavy drinking is based on measures of heavy alcohol use and binge drinking, which differs across participants’ sex and age. To fulfill the sample inclusion criteria, adolescents should be a heavy alcohol user and/or a binge drinker. However, problem drinkers who show symptoms of alcohol abuse or dependence (that is, an AUDIT score of 20 or above [29]) and/or of receiving treatment for alcohol-related problems will be excluded from participation since the WDYD intervention focuses on the prevention of heavy drinking rather than the prevention of problem drinking. The Ethical Committee (ECG) of the Faculty of Social Sciences of Radboud University Nijmegen in the Netherlands has approved the trial protocol.

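### The main-effect regressions name no baseline drinking term and allow only for class nesting, and the plan leaves open whether change or follow-up level is analysed

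*Protocol article*

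**What the plan says.** The Statistical methods section of the protocol article gives the model family, the outcomes and the time points: "Logistic and linear regressions will be performed in both the intention-to-treat and the completers-only analyses to test how the WDYD intervention is related" to heavy drinking, weekly consumption and binge frequency one and six months after the intervention. The only dependence it says will be handled is that of participants within classes. Age, sex and drinking status appear as moderators, in analyses additional to the main effects. The planned balance check concerns demographic characteristics. No covariates are listed for the main-effect models.

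Three other sections bear on this:

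- **Randomization:** "Randomization will occur by class level within the educational institutions to avoid contamination between the conditions". Blocks of four are used, and allocation follows the baseline assessment.
- **Outcomes:** the second primary outcome is "reductions in mean weekly alcohol consumption". The third is the frequency of binge drinking, with no reference to change.
- **Procedure and participants:** an online baseline assessment decides who enters the sample. Among other criteria, participants must "report heavy drinking in the past six months".

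**The concern.** Baseline drinking is likely to be among the strongest available predictors of later drinking, and it is measured before allocation. A main-effect model without it leaves explainable variance in the error and does nothing about chance imbalance in drinking between the arms. The planned balance check, as described, would not show such an imbalance.

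The outcome wording adds an ambiguity. The Outcomes section speaks of reductions, while the Statistical methods section speaks of weekly consumption at each follow-up. Three analyses fit: follow-up level alone, change from baseline, and follow-up level adjusted for baseline. They differ in precision, and the choice among them should not be open once data are in hand.

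Institution is a level of the randomisation but is absent where the analysis describes its data structure. VMBO precedes MBO in the school system, so the two types should differ in age, and the low-risk limits in the Objectives and hypotheses section change at age 17. Differences between institutions in the outcomes are therefore plausible, and a class-only model leaves them in the error.

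**Working it through.** **1. The plan's own figure, as context.** Inputs from the Sample size section: "42% in the experimental group versus 31% in the control group", a "two-sided test at alpha = 0.05, a power of (1-beta) = 0.80", and 15% loss. The usual two-proportion formula gives 300 per arm, or 318 with continuity correction.

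- With correction: 318/0.85 = 374.1, rounded up to 375 per arm, 750 in total. This matches the stated size with no design effect.
- Without correction: 300/0.85 = 352.9, rounded up to 353 per arm, 706 in total. Completers number 375 × 0.85 = 318.75 per arm, which leaves room for a design effect of 318.75/300 = 1.0625. With the design effect equal to 1 + (m − 1) × ICC, that is m = 1 + 0.0625/0.03 = 3.1 analysed participants per class at the lower stated ICC, or 1 + 0.0625/0.06 = 2.0 at the upper.

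No class size is given. If m were 10 (an assumption), the design effect would be 1.27 at ICC 0.03 or 1.54 at ICC 0.06, and power would be about 73% or 64%.

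**2. Precision for weekly consumption.** The input r, the correlation between baseline and follow-up consumption, is not in the article. I assume 0.4 to 0.6, equal variances at the two times, and no clustering. Relative to an unadjusted follow-up comparison, the variance of the effect is

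- change score: 2(1 − r);
- follow-up adjusted for baseline: 1 − r².

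Adjusted against change is (1 − r²)/[2(1 − r)] = (1 + r)/2.

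| r | change / unadjusted | adjusted / unadjusted | adjusted / change |
|---|---|---|---|
| 0.4 | 1.20 | 0.84 | 0.70 |
| 0.5 | 1.00 | 0.75 | 0.75 |
| 0.6 | 0.80 | 0.64 | 0.80 |

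Adjustment saves 16 to 36% of the variance against the unadjusted comparison, equivalent to 1/0.84 = 1.19 to 1/0.64 = 1.56 times the participants. It saves 20 to 30% against a change score. The change score is worse than no adjustment only for r below 0.5. Adjustment is better than both throughout the range.

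**3. Low-risk drinking.** These ratios do not carry over to a logistic model. There, adjustment does not shrink the standard error of the log odds ratio; it raises power because the conditional effect lies further from the null. The article gives nothing from which to size that gain.

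Baseline low-risk status is also a poor covariate to rely on. Entry requires heavy or binge drinking, which makes that status close to constant. It may not be fully constant, because entry looks back six months while the outcome items cover the previous week or month, but no figure is given. Baseline weekly consumption and binge frequency vary among those eligible and are the better covariates.

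**4. Institution.** No number of institutions and no institution-level correlation is stated, so the gain cannot be computed. If both arms are represented within institutions, differences between institutions largely cancel from the comparison. A class-only model still counts them as class variance, so its standard errors would mainly be too large.

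**The case against.** The strongest objection is that a journal article names a model family and leaves the covariates to a fuller document. The Statistical methods section neither includes nor excludes baseline drinking or institution, and the reductions wording points to some use of baseline. This stands in part. A reader might infer that the trial will ignore baseline drinking; the article does not say so. What remains is that the section goes into detail elsewhere (imputation method by data type, named moderators, mediation steps) and gives baseline drinking a role only as a moderator. Followed literally, its main-effect models are unadjusted. The mismatch between reductions and follow-up values is in the text itself.

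A second objection is that the size rests on an assumed correlation and on formulas for individually randomised data. That stands. In a cluster trial the saving depends on the correlations between and within classes, so it may be larger or smaller than shown.

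Three stronger readings are tempting and not supported:

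- **That the trial is already short of its stated power, so this omission makes a known deficit worse.** The shortfall depends on an unstated class size, and the Sample size section says that clustering was taken into account. The stated power also concerns the binary outcome, for which no gain is shown here.
- **That there are few randomised classes.** No number is given, and institutions are asked for as many classes as possible.
- **That leaving out institution invalidates the inference.** The likely effect is conservative standard errors. The article also does not say outright that the blocks of four are formed separately in each institution.

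**Conclusion.** The point holds as one about an under-specified and, taken literally, inefficient primary analysis. It does not show a biased or invalid one. For weekly consumption the avoidable loss is 16 to 36% of the variance against an unadjusted comparison and 20 to 30% against a change score. This assumes r of 0.4 to 0.6, equal variances and no clustering. For binge frequency a gain in the same direction is expected, but I have not sized it. For low-risk drinking and for institution no figure can be given from the article, and for institution the stake is precision. Because the improvement should need no new data, it is worth making whatever the class size proves to be.

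**What to change.** Name the following as the primary analysis:

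- **Weekly consumption and binge frequency:** model the follow-up value, not the change, adjusted for the baseline value of the same outcome.
- **Low-risk drinking:** logistic model adjusted for baseline weekly consumption and baseline binge frequency.
- **All three outcomes:** include institution, or a VMBO/MBO stratum where institutions are too small, with class as a random effect or class-robust standard errors.
- **Wording:** make the Outcomes and Statistical methods sections agree on what is analysed, so that a reduction is understood as a lower follow-up level given baseline.

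The cost is analysis wording only, provided that the baseline assessment uses the same consumption and binge items as the follow-ups. The article implies this without stating it item by item, and the figure that lists the measurements is not shown, so it should be confirmed. If it does not, the baseline drinking measures used for eligibility can serve as covariates, probably with a smaller gain.
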